### 9.9. Causality

For every AE, an interpretation of the causal relationship of the intervention to the AE in question will be made, based on the type of event; the relationship of the event to the time of vaccine administration; and the known biology of the vaccine therapy (**Error! Reference source not found.10**). Alternative causes of the AE, such as the natural history of pre-existing medical conditions, concomitant therapy, other risk factors and the temporal relationship of the event to vaccination will be considered and investigated. Causality assessment will take place during planned safety reviews, interim analyses (e.g. if a holding or stopping rule is activated) and at the final safety analysis, except for SAEs, which should be assigned by the reporting investigator, immediately, as described in SOP OVC005 Safety Reporting for CTIMPs.

Table 10: Assessment of causality

|   |                        |                                                                                                                                                                                                                                                |
|---|------------------------|------------------------------------------------------------------------------------------------------------------------------------------------------------------------------------------------------------------------------------------------|
| 0 | No Relationship | No temporal relationship to study product and
Alternate aetiology (clinical state, environmental or other interventions); and
Does not follow known pattern of response to study product                                   |
| 1 | Unlikely        | Unlikely temporal relationship to study product and
Alternate aetiology likely (clinical state, environmental or other interventions) and
Does not follow known typical or plausible pattern of response to study product. |
| 2 | Possible        | Reasonable temporal relationship to study product; or
Event not readily produced by clinical state, environmental or other interventions; or
Similar pattern of response to that seen with other vaccines                  |
| 3 | Probable        | Reasonable temporal relationship to study product; and
Event not readily produced by clinical state, environment, or other interventions or
Known pattern of response seen with other vaccines                             |
| 4 | Definite        | Reasonable temporal relationship to study product; and
Event not readily produced by clinical state, environment, or other interventions; and
Known pattern of response seen with other vaccines                           |

### 9.10. Reporting Procedures for All Adverse Events

All local and systemic AEs occurring in the 28 days following each vaccination observed by the Investigator or reported by the participant, whether or not attributed to study medication, will be recorded in electronic diaries or study database. All AEs that result in a participant's withdrawal from the study will be followed up until a satisfactory resolution occurs, or until a non-study related causality is assigned (if the participant consents to this). SAEs and Adverse Events of Special Interest (as outlined in Table 9) will be collected throughout the entire trial period.

The severity of clinical adverse events will be assessed according to scales based on FDA toxicity grading scales for healthy adolescents and children enrolled in preventive vaccine clinical trials. Severity grading criteria for temperature readings are given for adolescents. The normal ranges for a tympanic temperature in children aged 6-11 years is **35.8-38.0 C** (severity grading criteria not available).

Safety bloods will be assessed in accordance with normal ranges. Local sites will be responsible for following up any abnormal blood results the reference range which are of clinical concern. Severity grading scores are shown in Table 11, based on guidance from the Department of Aids (DAIDs) and OUH NHS Trust [37-38]

## CONFIDENTIAL

| Test              |      | Units               | Normal range                                                         | Grade 0            | Grade 1            | Grade 2           | Grade 3           |
|-------------------|------|---------------------|----------------------------------------------------------------------|--------------------|--------------------|-------------------|-------------------|
| FBC               |      |                     |                                                                      |                    |                    |                   |                   |
| Haemoglobin       |      | g/l                 | 115-155                                                              | 109-155            | 100-108            | 85-99             | <85               |
| White Blood Cells | Low  | x10  /L | 5 - 13                                                               | 4.51- 13.49        | 13.5 – 17.00       | 17.01 -22.00      | >22.00            |
|                   | High | x10  /L |                                                                      |                    | 3.5-4.5            | 2.5-3.49          | <2.5              |
| Platelets         |      | x10  /L | 150-450                                                              | 136-400            | 123-135            | 100-124           | <100              |
| Neutrophils       |      | x10  /L | 2.0 -8.0                                                             | 1.5-8.0            | 1.0-1.49           | 0.5-0.99          | <0.5              |
| Lymphocytes       |      | x10  /L | 1.0 -5.0                                                             | 1.0-5.0            | 0.75-0.99          | 0.50-0.74         | <0.5              |
| Eosinophils       |      | x10  /L | 0.1-1.0                                                              | 0.1-1.15           | 1.15-2.0           | 2.0 – 5.0         | >5.0              |
| INR               |      |                     | 1.0-1.1                                                              | 1.1 to < 1.5 x ULN | 1.5 to < 2.0 x ULN | 2.0 < x ULN       |                   |
| D Dimer           |      |                     | <500ng/ml                                                            |                    |                    |                   | >0.5ng/ml         |
| Biochemistry      |      |                     |                                                                      |                    |                    |                   |                   |
| Sodium            | Low  | mmol/l              | 135 - 145                                                            | 135 -146           | 147-148            | 149-150           | > 150             |
|                   | High | mmol/l              |                                                                      |                    | 132-134            | 130-131           | < 130             |
| Potassium         | Low  | mmol/l              | 3.5 - 5.0                                                            | 3.4 - 5.0          | 3.2-3.3            | 3.1               | 2.5-3.0           |
|                   | High | mmol/l              |                                                                      |                    | 5.1-5.2            | 5.3-5.4           | 5.5-6.5           |
| Urea              |      | mmol/l              | 2.5 – 6.0                                                            | 6.0-6.8            | 6.8-7.9            | 8.0-9.5           | >9.5              |
| Creatinine        |      | μmol/l              | 5-6 yrs: 25-42
7-8 yrs: 30-48
9-10 yrs: 28-57
11 yrs: 36-64 | Up to 1.1x ULN     | 1.1-1.5 x ULN      | >1.5 – 2 x ULN    | >2-3xULN          |
| Bilirubin         |      | μmol/l              | 0 -21                                                                | Up to 1.1x ULN     | 1.1 – 1.6 x ULN    | 1.6-2.6 x ULN     | >2.6xULN          |
| ALT               |      | IU/L                | 10 - 45                                                              | 1.1x ULN 45-49     | 1.1-2.5xULN 49-112 | >2-.5xULN 113-225 | >5-10xULN 226-450 |

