| Primary
To assess the safety, tolerability and reactogenicity profile of a prime-boost regimen (with an interval between prime and boost of 28 OR 112 days in 12-17 year olds, and interval of 112 days in 6-11 year olds) of the candidate vaccine ChAdOx1 nCoV-19 ( $5.0 \times 10^{10}$ vp / $5.0 \times 10^{10}$ vp) in children aged 6-17 years. | a) occurrence of solicited local reactogenicity signs and symptoms for 7 days following vaccination;
b) occurrence of solicited systemic reactogenicity signs and symptoms for 7 days following vaccination;
c) occurrence of unsolicited adverse events (AEs) for 28 days following vaccination;
d) occurrence of SAEs and disease enhancement episodes
e) occurrence of abnormal laboratory findings (Grade 3 and above) | a)-c) as stated, d) throughout the study, e) D2 and D7 post-boost blood tests (safety bloods) |
| Secondary
To assess cellular and humoral immunogenicity of ChAdOx1 nCoV-19 ( $5.0 \times 10^{10}$ vp / $5.0 \times 10^{10}$ vp) given as homologous prime boost (at 28 and 112 days post prime in 12-17 year olds, and 112 days post prime in children aged 6-11 years)                                                                               | a) Quantify antibodies against SARS-CoV-2 spike protein (seroconversion rates)
b) Virus neutralising antibody (NAb) assays against live and/or pseudotype SARS-CoV-2 virus
c) Interferon-gamma (IFN- $\gamma$ ) enzyme-linked immunospot (ELISpot) responses to SARS-CoV-2 spike protein
d) cell analysis by flow cytometry assays                                                                                            | Blood samples drawn at D0, D28, D56, , D84, D112, D140, D182 and 364                          |

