### 7.3. Blood tests

Safety bloods will be taken for a subset of up to 40 participants in groups 3 and 4, as outlined in tables 5b and 5d. These will include a full blood count, urea and electrolytes, liver function tests, CRP, clotting screen and D-dimer. Reference ranges will be in accordance with local NHS guidelines. Abnormalities occurring outside this range will be graded in severity and those scoring a grade 3 or above will be classified as an AE.

Immunology; Immunogenicity will be assessed by a variety of immunological assays. This may include antibodies to SARS-CoV-Spike and non-Spike antigens by ELISA, ex vivo ELISpot assays for interferon gamma and flow cytometry assays, neutralising and other functional antibody assays and B cell analyses, virus neutralising Ab (NAb) assays against live and/or pseudotype SARS-CoV-2 virus. Other exploratory immunological assays including cytokine analysis and other antibody assays, DNA analysis of genetic polymorphisms potentially relevant to vaccine immunogenicity and gene expression studies amongst others may be performed at the discretion of the Investigators. Further exploratory immunology assays may be performed at the discretion of the Investigators on HIV and non-HIV cohorts, including, but not limited to: T cell Proliferative responses to SARS-CoV-2 antigen; T cell cross-reactivity to circulating common cold coronaviruses; Multiparameter immunophenotyping by CyTOF; BCR and TCR repertoire analysis; Serum analysis by Luminex (including inflammatory, anti-inflammatory and adaptive cytokines, chemokines, growth factors and antimicrobial proteins); HIV viral reservoir; amongst others.

Collaboration with other specialist laboratories in the UK, Europe and outside of Europe for further exploratory tests may occur. This would involve the transfer of serum or plasma, PBMC and/or other study samples to these laboratories, but these would remain anonymised. Informed consent for this will be gained from participants. This would be in line with the national guidance and policy for submitting samples for testing at reference labs. Immunological assays will be conducted according to local SOPs.

Participants or their parent/guardian will be informed that there may be leftover samples of their blood (after all testing for this study is completed), and that such samples may be stored indefinitely for possible

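### Primary endpoint (e) counts laboratory findings of Grade 3 or higher, but Table 11 leaves ALT, creatinine and potassium values beyond its Grade 3 limits ungraded and, as printed, gives INR no Grade 3

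*Protocol*

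**What the plan says.** Section 4 (and the Synopsis) lists as a primary outcome "e) occurrence of abnormal laboratory findings (Grade 3 and above"), assessed at "e) D2 and D7 post-boost blood tests (safety bloods"). Section 7.3 (Blood tests) defines the sample and the panel: "Safety bloods will be taken for a subset of up to 40 participants in groups 3 and 4", covering "full blood count, urea and electrolytes, liver function tests, CRP, clotting screen and D-dimer". It adds that abnormal results are graded and that "those scoring a grade 3 or above will be classified as an AE".

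Section 9.10 points to Table 11 for laboratory severity grades. Its columns run from Grade 0 to Grade 3. Four entries matter here:

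- ALT, Grade 3: ">5-10xULN 226-450".
- Creatinine, Grade 3: above 2 and up to 3 times ULN.
- Potassium, Grade 3: 2.5-3.0 mmol/l on the low side and 5.5-6.5 mmol/l on the high side.
- INR, Grades 0, 1 and 2: "1.1 to < 1.5 x ULN | 1.5 to < 2.0 x ULN | 2.0 < x ULN". The Grade 3 cell is empty.

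The scales for local events, fever and general events in Tables 12 to 14 do define a Grade 4.

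**The concern.** The endpoint is worded for a scale with something at or above Grade 3, but the laboratory scale ends at Grade 3 and in places closes that grade at its outer limit. Taken literally, a moderately severe result is counted while a more severe one has no grade. Two analysts, or two sites, could handle such a result differently and both claim to follow the protocol.

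INR is a different case. As printed, its top category is labelled Grade 2, so even a very high INR is graded and falls short of the endpoint. Protocol version 6.0 added clotting tests to the safety bloods and amended the grading table for them, following the April 2021 JCVI guidance on clot risk. INR is therefore one of the measurements that change was meant to bring in.

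The grade is also used elsewhere. The group holding rule for unsolicited events (Section 9.17.1) and the individual stopping rule for unsolicited events (Section 9.17.2) both refer to Grade 3. A laboratory event without a grade leaves it unclear whether they apply.

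**Working it through.** **Inputs.** All come from Table 11: ALT normal range 10-45 IU/L; creatinine upper limits 42, 48, 57 and 64 µmol/l for ages 5-6, 7-8, 9-10 and 11; INR normal range 1.0-1.1; and the printed Grade 3 cells.

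**Step 1: is the ALT ceiling real?** With ULN = 45, 5 × 45 = 225 and 10 × 45 = 450. The printed band for more than 5 and up to 10 times ULN is 226-450, so the plan's figure is reproduced. The upper limit is given both as a multiple and in units, so it is not a lost inequality sign.

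**Step 2: where does Grade 3 end?**

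| Analyte | Printed Grade 3 | No grade |
|---|---|---|
| ALT | 226-450 IU/L | above 450 |
| Creatinine, age 5-6 | above 84, to 126 µmol/l (2 × 42, 3 × 42) | above 126 |
| Creatinine, age 7-8 | above 96, to 144 (2 × 48, 3 × 48) | above 144 |
| Creatinine, age 9-10 | above 114, to 171 (2 × 57, 3 × 57) | above 171 |
| Creatinine, age 11 | above 128, to 192 (2 × 64, 3 × 64) | above 192 |
| Potassium, low | 2.5-3.0 mmol/l | below 2.5 |
| Potassium, high | 5.5-6.5 mmol/l | above 6.5 |

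Examples: ALT 400 is Grade 3, ALT 500 has no grade. Creatinine 150 at age 11 is Grade 3, 200 has no grade. Potassium 6.0 is Grade 3, 7.0 has no grade; 2.7 is Grade 3, 2.3 has no grade.

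**Step 3: INR as printed.** The top category starts at 2.0 × 1.1 = 2.2 and sits under Grade 2. An INR of 5 is 5 / 1.1 = 4.5 times ULN and is still Grade 2. No INR reaches Grade 3.

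**Step 4: is this a convention of the table?** I counted each analyte once, or twice where both directions are graded, giving 20 graded directions. Fifteen have an open-ended Grade 3, for example bilirubin above 2.6 times ULN, urea above 9.5, CRP above 100 and platelets below 100. Four are closed: ALT, creatinine, low potassium and high potassium. One, INR, has no Grade 3. 15 + 4 + 1 = 20. The table follows no single rule that would tell a reader how to treat values past a closed band.

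**Step 5: how much can one result matter?** Tables 5c and 5d allocate 10 children to each of four post-boost visits, and each child attends only one: 4 × 10 = 40, matching the stated maximum. With all 40 sampled, one child left out of the count changes the overall figure from 1/40 = 2.5% to 0.

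**The case against.** The strongest reply is that nothing excludes these values. Both the endpoint and Section 7.3 speak of Grade 3 or higher, and a value beyond the Grade 3 ceiling is higher in the ordinary sense. That is fair for ALT, creatinine and potassium: such results are ungraded, not ruled out. A reader might infer that the protocol drops its worst liver, kidney and potassium results from the endpoint, but the text does not go that far. What remains is that the sensible reading is not written down.

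A reader might also infer that these results escape adverse-event recording, or that a coagulopathy shown by INR could not be recorded. The protocol does not support either inference. Section 7.3 says results at Grade 3 or higher are adverse events, but not that only those are. Section 9.1 includes any clinically significant abnormal laboratory finding, with no grade threshold. Coagulopathy, acute liver injury and acute kidney injury are AESIs in Table 9, collected throughout the trial (Section 9.10) and reported to the DSMB if not already SAEs (Section 9.11).

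The INR row could also be misaligned, by the authors or when the PDF was read. It has three entries for four grade columns, and its Grade 0 runs to 1.5 times ULN, whereas creatinine, bilirubin, ALT and ALP end Grade 0 at 1.1 times ULN. If the row moves one column to the right, its top category becomes an open-ended Grade 3 and the INR point disappears. Against that, the adjacent D-dimer row kept its blank cells, and urea, ALT and ALP also start Grade 0 at or above ULN, as the INR row does. The question stays open; the other three analytes do not depend on it.

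Lastly, the endpoint is descriptive, the children are healthy, and low platelets already have an open-ended Grade 3. This limits the practical effect but does not settle how an extreme result would be counted. Nor can it be left to the SAP, because the protocol itself fixes both the threshold and the table.

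**Conclusion.** The point stands as a mismatch between a primary endpoint and its grading scale. For ALT, creatinine and potassium (four of 20 graded directions), values beyond the printed Grade 3 range have no grade, so their place in endpoint (e) is undefined. For INR, as printed, no result can count; this rests on the row being aligned in the source document as it appears here.

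The consequence is confined to the endpoint (e) count and to the holding and stopping rules that refer to Grade 3. Few results of this kind are expected among at most 40 healthy children. The documents give no rate from which to estimate how many, so the only size that can be stated is that one uncounted child shifts the overall figure from 2.5% to 0 when all 40 are sampled. It would be wrong to conclude that a reported zero must be an artefact of the scale, or that serious abnormalities would go unrecorded. The defect is worth correcting because it is cheap to remove and concerns a primary safety outcome.

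**What to change.** Add one sentence to the definition of endpoint (e) and to Section 7.3, stating that any value at or beyond the printed Grade 3 boundary counts as Grade 3 or higher. Alternatively, add a Grade 4 column to Table 11 for the analytes whose Grade 3 is closed. The sponsor should check the INR row against its source scale and reconcile it so that it has a Grade 3 entry; this review proposes no cut-off. The protocol should also say how a result beyond the printed range is treated in the Grade 3 rules of Sections 9.17.1 and 9.17.2, again without this review suggesting what those rules should be.

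The cost is a few corrected table cells and a short clarification. No new data are needed, because Section 11.3 already has blood results recorded in the CRF, so results can be graded again from the recorded values.

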## CONFIDENTIAL

|         |  |      |                                                                    |             |              |                |         |
|---------|--|------|--------------------------------------------------------------------|-------------|--------------|----------------|---------|
| ALP     |  | IU/L | 6-10 yrs: 135-557
11-14yr (Boy) 92-549
11-14yr (Girl) 50-415 | 1-1.1 x ULN | 1.1 – 2x ULN | >2.5 – 5 x ULN | >5x ULN |
| Albumin |  | g/l  | 32-50                                                              | 28-32       | 28-32        | 25-27          | <25     |
| CRP     |  | mg/l | <10                                                                | <10         | 10-3-        | 31-100         | >100    |

Table 11: severity grading scales for abnormal blood results , ULN = upper limit of normal

Table 12. Severity grading criteria for local adverse events \*erythema  $\leq 2.5$ cm is an expected consequence of skin puncture and will therefore not be considered an adverse event

| Adverse Event                         | Grade | Intensity                                       |
|---------------------------------------|-------|-------------------------------------------------|
| Pain at injection site                | 1     | Pain that is easily tolerated                   |
|                                       | 2     | Pain that interferes with daily activity        |
|                                       | 3     | Pain that prevents daily activity               |
|                                       | 4     | A&E visit or hospitalization                    |
| Tenderness                            | 1     | Mild discomfort to touch                        |
|                                       | 2     | Discomfort with movement                        |
|                                       | 3     | Significant discomfort at rest                  |
|                                       | 4     | A&E visit or hospitalization                    |
| Erythema at injection site*           | 1     | 2.5 - 5 cm                                      |
|                                       | 2     | 5.1 - 10 cm                                     |
|                                       | 3     | >10 cm                                          |
|                                       | 4     | Necrosis or exfoliative dermatitis              |
| Induration/Swelling at injection site | 1     | 2.5 – 5 cm and does not interfere with activity |
|                                       | 2     | 5.1 - 10 cm or interferes with activity         |
|                                       | 3     | >10 cm or prevents daily activity               |
|                                       | 4     | Necrosis                                        |

| Vital Signs  | Grade 1
(mild) | Grade 2
(moderate) | Grade 3
(severe) | Grade 4
Potentially
Life
threatening |
|--------------|-------------------|-----------------------|---------------------|-----------------------------------------------|
| Fever (oral) | 38.0°C - 38.4°C   | 38.5°C – 38.9°C       | 39.0°C - 40°C       | > 40°C                                        |

